Regarding home titration of antihypertensive medication, evidence is more limited and shows mixed results. Two clinical essays, the TASMINT2 (15) and the TASMINT-SR (16), both in the United Kingdom and developed in the primary care setting by the same research team, are some of the most recent and interesting clinical trials carried out in this field. In these studies, SMBP together with self-titrate medications (according to a previously agreed plan), combined with telemedicine components, was compared with usual care. In both studies systolic blood pressure (SBP) decreased from baseline to 12 months, with significant differences between the intervention and control group (5.4 and 9.2 mmHg, respectively). Frequency of side effects was similar in both groups (15,16). The TASMINT-SR study is of special relevance because it was carried out with high-risk patients (with a personal history of stroke, ischemic cardiopathy, diabetes or kidney failure), a population of special interest to achieve BP targets (16). On the other hand, a clinical trial carried out in the US in a low-income, predominantly minority population, aimed to determine whether health coaching, SMBP and home titration of antihypertensive medications could improve BP control compared with SMBP and health coaching alone. The results showed that both the home-titration arm and the no-home-

titration arm had a reduction in SBP, with no significant differences between them from baseline to 6 months (17).

Finally, when interpreting hypertension studies over time, it is important to proceed with caution, as the definition of the condition changes almost with every update of guidance. For instance, earlier versions of guidelines such as those of the Joint National Committee (JNC) and of the European Society of Hypertension (ESH)/European Society of Cardiology (ESC), suggested more restrictive BP control objectives than recent versions (especially in patients over 60 years old, diabetics and patients with renal failure)(18-20). These objectives may be modified again in the light of the results of recent studies (21-23).

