### **5.2 Objectives**

1. To evaluate the effectiveness of an intervention based on self-monitoring and self-adjustment of medication in poorly controlled hypertensive patients.
2. Evaluate its impact on adherence to treatments, lifestyles, quality of life, the occurrence of adverse events, the use of health services, and the costs of care.
3. Estimate its efficiency (cost-effectiveness).
4. Evaluate the views and experiences of patients, caregivers and health professionals about self-management, self-monitoring and self-adjustment of antihypertensive medication

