## 10. SAFETY ASSESSMENT

The ADAMPA study is a clinical trial carried out under naturalistic conditions where the intervention is based on self-monitoring and self-adjustment of medication in poorly controlled hypertensive patients. The antihypertensive drugs used will be those that patients are taking as part of their usual medication. It is considered a low-risk clinical trial, and no differences in adverse events are expected compared to usual medical practice. Therefore, the need for a safety committee has not been anticipated. The reference safety information will be the technical data sheets of each of the antihypertensive drugs. Consequently, it is the investigator's responsibility to detect and document any event that meets the criteria and definitions of adverse events (AE) or serious adverse events (SAE), especially when such events are not described in the technical sheet.

During the study, the existence of adverse events, whether serious or not, will be checked according to the definitions provided in this section of the protocol. The Sponsor will be responsible for promptly notifying Health Authorities, such as the Spanish Agency for Medicines and Health Products (AEMPS), and Autonomous Communities (CCAA) if applicable, about serious and unexpected adverse reactions (RAGI), annual reports, or any other relevant

safety information. Additionally, the Sponsor will be responsible for notifying researchers about safety information.

a) Definitions:

**Adverse event (AE)** Refers to any harmful incident to a patient or clinical trial subject treated with a drug, even if it doesn't necessarily have a causal relationship with the treatment.

**Adverse reaction (AR):** Denotes any harmful and unintentional reaction to an investigational drug, regardless of the administered dose.

**Serious adverse event (SAE):** Encompasses adverse events that, at any dose, cause death, threaten the subject's life, require hospitalization or its prolongation, result in permanent or significant disability, disability, or give rise to a congenital anomaly or malformation. For notification purposes, suspected adverse events considered important from a medical perspective will also be treated as serious, even if they don't fully meet the above criteria.

**Serious and Unexpected Adverse Reaction (GUAR):** Represents an adverse reaction whose nature or severity doesn't correspond to the information in the product's technical data sheet.

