**Causality criteria:**

The establishment of a causal relationship between the antihypertensive drug and the occurrence of AA/AAG will be based on clinical judgment. To achieve this, other potential causes will be considered and studied, including the natural progression of the underlying diseases, concurrent treatments, other risk factors, and the temporal correlation of the event with the investigational product. The technical data sheet of the drug will serve as the reference safety information for this study.

**Related adverse event:** The temporal correlation between AE and the antihypertensive drug indicates a possible causal relationship, which cannot be explained by factors such as the patient's clinical status or therapeutic interventions.

**Unrelated adverse event:** The temporal relationship between the adverse event (AE) and the antihypertensive drug suggests an unlikely causal connection. Alternatively, other factors (medications or concurrent conditions) and additional therapeutic interventions may offer a satisfactory explanation for the AE.

b) Information on adverse events

**Detection method:** Adverse events will be recorded from the informed consent stage and at each visit through careful clinical observation, patient communication, and open questioning by the investigator.

**Record of adverse events:** All AEs and AAEs not mentioned in the data sheet must be documented in the clinical history and CRD. This documentation will include start and end dates, event descriptions, severity, evolution, outcome, relationship with the antihypertensive drug, and measures taken. At each visit, all AEs that the patient has experienced since the previous visit must be documented on the Adverse Events Form, provided they are not already included in the technical file. If an adverse event was pre-existing and has worsened in terms of intensity or frequency, the direction of the change should be indicated.

c) Procedures for immediate notification of serious or unexpected adverse events

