**Prompt reporting of serious adverse events by the investigator**

In the event of an SAE, the investigator will inform the pharmacovigilance unit within 24 hours of becoming aware of it.

The initial communication of the SAAs must be in writing using the provided Serious Adverse Events Notification Form provided by the Unit responsible for the pharmacovigilance of the trial (**ANNEX 1**). The form must be sent via email to: [contact].

The person in charge of Pharmacovigilance will review the received form and, if necessary, request additional information from the investigator. The investigator will provide this information when requested and, if there are changes in their initial assessment of severity or causation, will communicate these changes. The notification procedure described earlier will be followed for conveying monitoring information. The person in charge of Pharmacovigilance will maintain a detailed record of all SAEs or significant events communicated by researchers.

Deaths of subjects participating in the study must be notified using the notification form within 24 hours of knowledge of the death, as long as the subject is within the follow-up period.

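### Section 10 b) lets adverse events already in a drug's data sheet stay off the Adverse Events Form, contrary to the rest of the protocol, so non-serious known drug effects may go unrecorded

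*Protocol*

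**What the plan says.** Section 10 and Table 2 deal with the recording of adverse events in several places.

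- **General duty (section 10, opening).** The investigator must "detect and document any event that meets the criteria and definitions of adverse events (AE) or serious adverse events (SAE"). Events absent from the technical sheet are singled out for special attention, but the duty is not confined to them. The next paragraph says that both serious and non-serious events will be checked.
- **Reference document (same place).** "The reference safety information will be the technical data sheets of each of the antihypertensive drugs".
- **Detection (section 10 b).** "Adverse events will be recorded from the informed consent stage and at each visit", with no condition about the data sheet.
- **Visit schedule (section 6.6, Table 2).** Adverse events are a data item at 6, 12 and 24 months, without qualification.
- **Recording (section 10 b).** "All AEs and AAEs not mentioned in the data sheet must be documented in the clinical history and CRD". For each visit, the events since the previous one "must be documented on the Adverse Events Form, provided they are not already included in the technical file".

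Objective 2 in section 5.2 includes evaluating the intervention's impact on "the occurrence of adverse events, the use of health services, and the costs of care".

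**The concern.** The recording paragraph turns the data sheet into a filter on what is written down. Elsewhere in section 10 the data sheet has a different and conventional use: it decides whether a serious reaction is unexpected and so needs expedited reporting.

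The filter falls on the wrong events for this trial. The intervention has patients adjust their own antihypertensive treatment (section 6.4.1). If that does harm short of a serious event, the likeliest form is a known effect of a known drug, which by definition is already in the data sheet. The background cites two earlier self-titration trials in which "Frequency of side effects was similar in both groups", and section 10 expects no difference in adverse events from usual practice. A record without listed effects could not show whether that holds here for non-serious effects.

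This is a rule about data collection. No later analysis plan can recover events that were never recorded.

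**Working it through.** The protocol gives no rate for non-serious adverse events, so there is no figure to reproduce. The check sets the provisions side by side.

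**1. Is the conflict real?** The opening of section 10 covers every event that meets the definition and stresses unlisted ones. The form sentence in section 10 b) admits only unlisted ones. An investigator who meets a non-serious, listed effect is told by the first to document it and is not required by the second to enter it on the form. The form sentence has only one reading.

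**2. Does the exemption also reach the CRD?** This is less clear. In "All AEs and AAEs not mentioned in the data sheet must be documented in the clinical history and CRD", the data-sheet qualifier may attach to both kinds of event or only to the second abbreviation, which the protocol does not define and which appears to mean serious events. On the first reading, listed events are required neither in the clinical history nor in the CRD. On the second, all adverse events go into the CRD and only the form leaves out listed ones. The protocol does not say whether the form is part of the CRD.

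**3. What do other provisions capture regardless of listing?**
- Serious events: for those needing immediate notification, "the investigator will inform the pharmacovigilance unit within 24 hours of becoming aware of it". The serious events excused from immediate notification must still go into the clinical history and CRD (section 10 c).
- Medically important suspected events: treated as serious for notification (section 10 a).
- Angina, myocardial infarction, stroke, hypotensive crisis and death: collected as a separate outcome (section 6.1.2; section 9.1, Table 4), including outpatient and emergency visits for hypotensive crises.

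**4. What is left?** Subtracting step 3 leaves non-serious, not medically important, listed effects other than hypotensive crises. Only the general duty, the detection sentence and Table 2 cover these, and the recording paragraph contradicts all three. No other provision clearly restores them.

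**5. Which planned results depend on them?** The planned between-arm comparison of adverse events is defined on the five clinical events, so it does not. Neither does systolic pressure at 12 months. What depends on them is any wider statement about tolerability under Objective 2. Section 10 c) expects combined event figures below 3% and does not anticipate detectable differences, so the securely collected events are, on the protocol's own account, too sparse to fill that gap.

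**The case against.** The strongest reply is that the protocol gives Objective 2 its own working definition. Sections 6.1.2 and 9.1 name five events and compare those, and no between-arm analysis of non-serious events is planned. This stands: the planned adverse-event outcome is intact. A reader might infer that the exemption invalidates it, and the documents do not support that.

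A second reply is that loss is not certain. Table 2, the general duty and the detection sentence all point towards full recording, and the CRD sentence can be read the same way. This also stands. The contradiction is established; the loss is likely under the form sentence, but not proven.

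A third reply is that lighter recording suits a low-intervention trial that does not set out to assess the safety of medicines (sections 8.1 and 13.2). Treatment changes, persistence, consultations and EQ-5D would also give indirect signals of poor tolerability. A risk-adapted rule would be defensible, but the opening of section 10 would then have to state it, and it now says the opposite. Indirect signals do not replace a record of the events.

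A reader might go further and infer a bias in favour of the intervention: if listing is judged against each patient's own drugs, the exemption depends on treatment after randomisation. The protocol does not say whose drugs' data sheets apply, and gives neither event rates nor listed shares by arm. Neither the direction nor the size of any bias can be supported. Nor do the documents show that recording would vary among the many physician-investigators, since the collaborating research physicians handle data collection at the scheduled visits (section 6.5).

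**Conclusion.** The point holds as a real inconsistency of limited reach. One rule in section 10 b) exempts listed adverse events from the Adverse Events Form, and on one reading from the CRD, while the rest of the protocol asks for all of them. Serious events, medically important events, the five-event outcome and the primary outcome are not touched. At stake are non-serious, listed drug effects, for which a trial following the restrictive rule would have no dependable record.

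That these are the most plausible harms of self-titration is an inference from how the intervention works; the protocol itself expects no difference. The size of the loss cannot be given, because it depends on event rates and listed shares that the protocol does not state and on which rule investigators follow. This is a minor correction, worth making because it is cheap and changes what is collected.

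**What to change.** In section 10 b), Record of adverse events, delete the data-sheet qualifier from the CRD sentence and the closing proviso from the form sentence. Every adverse event, listed or not, is then recorded on both the CRD and the form, in both arms, at the scheduled visits, as the opening of section 10 and Table 2 already imply. Keep the technical data sheet for one purpose: judging expectedness for the expedited notification of serious reactions in section 10 c).

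The cost is two deleted phrases and a few more entries per visit. If that burden is a worry, a short checklist of common listed effects, asked in the same words in both arms at 6, 12 and 24 months, is an option but not essential. Reporting would still be open-label, so any comparison of non-serious events should be read with that in mind.

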**Prompt reporting of serious adverse events by the investigator**

In the event of an SAE, the investigator will inform the pharmacovigilance unit within 24 hours of becoming aware of it.

The initial communication of the SAAs must be in writing using the provided Serious Adverse Events Notification Form provided by the Unit responsible for the pharmacovigilance of the trial (**ANNEX 1**). The form must be sent via email to: [contact].

The person in charge of Pharmacovigilance will review the received form and, if necessary, request additional information from the investigator. The investigator will provide this information when requested and, if there are changes in their initial assessment of severity or causation, will communicate these changes. The notification procedure described earlier will be followed for conveying monitoring information. The person in charge of Pharmacovigilance will maintain a detailed record of all SAEs or significant events communicated by researchers.

Deaths of subjects participating in the study must be notified using the notification form within 24 hours of knowledge of the death, as long as the subject is within the follow-up period.

**Serious adverse events that do not require immediate notification by the investigator**

The following serious adverse events do not require immediate notification by form:

- Thromboembolic events (deep vein thrombosis, pulmonary thromboembolism)
- Neurological events (stroke, cerebrovascular accident, acute confusional syndrome)
- Cardiological events (angina, myocardial infarction, cardiac arrhythmia, decompensation of heart failure, hypotensive crises)
- Impaired renal function
- Gastrointestinal bleeding
- Need for blood transfusion
- Hospitalization due to hydroelectrolyte disorder

In any case, there will be a section in the CRD to collect information on possible serious adverse events reported by the patient during follow-up visits. Serious adverse events that do not require immediate notification must be included in the clinical history and in the CRD, and will be included in the periodic safety report.

On the other hand, the study will collect data related to urgent hospital admissions due to episodes of angina, myocardial infarction, stroke, and hypotensive crises, as well as death from any cause, along with outpatient and emergency visits due to hypotensive crises, as part of the tertiary objectives of the study. Given the characteristics of the included population (and the results of the TASMINE-SR^17 study), figures of less than 3% are expected for the combined endpoints; therefore, it is not anticipated that differences will be detectable. For these serious events, as well as for deaths, the Family Physician Investigators responsible for the patients (MEFI) will review the medical history and determine their potential relationship with the intervention. Previous trials have failed to find any evidence of such a relationship.

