## **6.4 Intervention**

### **6.4.1 Intervention group**

The trial intervention is not pharmacological; instead, it involves modifying usual clinical practice. The intervention for self-monitoring and self-adjustment of medication consists of three key elements:

- 1) Patient training: This involves providing information and training on arterial hypertension, its associated risks, its management, the benefits of achieving adequate control, and general measures for improved control.
- 2) Training for self-monitoring: Patients will receive instruction on the correct method for ambulatory blood pressure monitoring (AMPA), as well as guidance on how to measure their blood pressure and record the values using the provided tools.
- 3) Training for self-adjustment: Patients will be educated about target blood pressure goals, individually tailored to each patient. They will also learn how to respond when faced with specific blood pressure readings, including the self-adjustment of their pharmacological treatment.

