For each patient, once it has been verified that the inclusion criteria are met and the exclusion criteria are not met, and once the informed consent is signed, the MEFI will enter into the web system and under mandatory guarantees of information security, the information of identification of the patients, marking the boxes corresponding to meeting the inclusion criteria and not meeting the exclusion criteria, and the information necessary for randomization with minimization (see 6.3.1 for more details on the minimization process). The MEFI will receive the result of the randomization and the anonymization code assigned to the patient via the Web, and the patient will be included in an electronic patient identification form with restricted access to Collaborating Research Physicians (MIC). The patient identification form will not contain any health data or other sensitive information. All the documents in which the data of the patients in the framework of the ADAMPA study are recorded (CDR, Patient's Notebook) will be identified only by the code assigned to each patient. Likewise, and in order to help their adequate follow-up and identification in the consultation, it will be indicated in the electronic medical record that the patient participates in the ADAMPA STUDY.

All patients, both those randomized to the control group and those in the intervention group, will receive information from the MEFI that a collaborating research physician (MIC team) will contact them by telephone to schedule the baseline visit.

Furthermore, the MEFI will provide all patients with an ADAMPA study Patient's Notebook. On the first page, the assigned patient code will be recorded. In the case of the intervention group, the MEFI will also note on the first page the arm in which the patient's blood pressure will be measured and their target figures. The Intervention Group Notebook will contain:

- First sheet: patient anonymization code, arm for blood pressure measurement, target figures
- Information about the importance of hypertension and lifestyle advice
- Instructions on how to take your blood pressure at home
- Instructions on how to act based on the voltage figures at home
- The medication self-adjustment plan established by the MEFI. The MEFI may establish the initial self-adjustment plan on that same visit or on another scheduled visit agreed upon with the patient.
- Sheets for recording BP values and for recording care contacts with your Health Center.

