#### 8.5.5 Treatment visit

Visits to modify treatment, if applicable, will be carried out in the usual context of clinical practice by the patient's family doctor (MEFI) in both the control and intervention groups.

Additionally, the patients of the Intervention group will make visits or telephone consultations to their MEFI when so indicated according to the mode of action according to blood pressure figures, in the event that they must proceed to self-adjust the medication according to the plan. self-adjustment established by the MEFI and registered in the patient's notebook.

In the event that a patient from the intervention group, and based on their objective figures and the instructions received, has to proceed to the self-adjustment at home, they will again follow the mandatory instructions and that are also included in the Patient's Notebook and You will request an appointment with your MEFI within a maximum period of three weeks. On said visit after self-adjustment, the MEFI will review the patient's condition and renew the self-adjustment plan, recording said new self-adjustment plan in the Patient's Notebook.

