| Differences in changes in lifestyles (smoking, exercise, weight) at 6, 12, and 24 months with respect to the baseline measurement.                            | Changes in lifestyles will be evaluated based on the information collected at follow-up visits.                                                                                                                                                                                                                                                                               |
| Difference between groups in relation to the occurrence of adverse events: angina, myocardial infarction, stroke, hypotensive crisis and death.               | Hospitalizations due to adverse events will be collected at follow-up visits. Outpatient and emergency visits due to hypotensive crises will also be collected.                                                                                                                                                                                                               |
| Differences in the use of health services during follow-up (6, 12 and 24 months).                                                                             | Including HTA-related primary medical and nursing care consultations (at the center by appointment or without an appointment, by telephone and at home). Visits to emergency hospital services, hospital admissions, hospitalization days per admission and main diagnosis                                                                                                    |
| Incremental cost per additional quality-adjusted life year gained in the intervention group compared to the control group.                                    | Cost-consequence analysis and cost-effectiveness analysis                                                                                                                                                                                                                                                                                                                     |

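### Hypotensive crisis is compared between arms partly on outpatient visits, but only the intervention arm is trained and instructed by the trial to measure BP at home and contact the physician on the figures, so detection can differ at equal true risk

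*Protocol*

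**What the plan says.** Table 4 (section 9.1) lists as a tertiary endpoint: "Difference between groups in relation to the occurrence of adverse events: angina, myocardial infarction, stroke, hypotensive crisis and death". The stated method is hospitalizations due to these events, with one addition for a single component: "Outpatient and emergency visits due to hypotensive crises will also be collected". Section 10 c), on serious events exempt from immediate notification, repeats this. Urgent admissions are collected for angina, infarction, stroke and hypotensive crisis, and deaths from any cause; for hypotensive crisis these are taken "along with outpatient and emergency visits due to hypotensive crises, as part of the tertiary objectives of the study". The same section expects less than 3% for the combined endpoints and does not anticipate a detectable difference.

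The arms differ in how a low reading comes to light:

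- **Intervention.** Section 6.4.1 provides training in home measurement, "as well as guidance on how to measure their blood pressure and record the values using the provided tools". The Patient's Notebook (section 8.5.1) contains "Instructions on how to act based on the voltage figures at home" and sheets for recording BP. Under section 8.5.5 these patients "will make visits or telephone consultations to their MEFI when so indicated according to the mode of action according to blood pressure figures", and after a self-adjustment the instruction is: "You will request an appointment with your MEFI within a maximum period of three weeks". Section 6.5 adds bi-monthly telephone calls in the first year.
- **Control.** Section 6.4.2 gives information about hypertension and no additional intervention. The control notebook (section 8.5.1) has sheets for care contacts, but no BP sheets and no instructions for acting on readings. Section 8.5.2 refers these patients to their usual check-ups.

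Both arms share the 6-, 12- and 24-month visits (section 8.4) and open questioning about adverse events at each visit (section 10 b).

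**The concern.** Admission for infarction or stroke depends little on whether the patient owns a monitor. An outpatient visit for low blood pressure may depend on it a good deal. The trial gives one arm the means to see a low reading and a routine for contacting the physician on readings. The same episode can then become a counted event in one arm and go unrecorded in the other. The protocol gives no blood pressure level, symptom or clinician-measured value for a hypotensive crisis, so the definition does not screen out this difference.

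Scheduled visits and open questioning are the same in both arms, but they do not equalise unscheduled contacts that arose because of the allocation. Taking the visits from the electronic record would not help either, since the visit itself may result from the allocation.

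Hypotension is the obvious harm to look for when patients adjust their own antihypertensives. As the event is collected, a modest intervention-arm excess could not be separated from better detection.

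**Working it through.** The protocol gives no figure for this bias, so there is none to reproduce. The calculation is an illustration.

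**Inputs from the protocol.** 458 randomized 1:1, so n = 229 per arm (section 1). Expected rate for the combined endpoints below 3% (section 10 c): 0.03 × 229 = 6.9, so at most about 7 patients per arm.

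**Assumed inputs.** Recorded rate in controls p_C = 1%, that is 0.01 × 229 = 2.3 patients. True risk is equal in both arms. A further δ of intervention patients have an outpatient visit that would not have been recorded without home measurement, so p_I = p_C + δ.

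**Method.** With X_I ~ Bin(229, p_I) and X_C ~ Bin(229, p_C), sum the joint probabilities over all pairs of counts to obtain P(X_I > X_C) and the probability that a two-sided Fisher test gives p < 0.05.

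**Results with p_C = 1%:**

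- δ = 0: 2.3 against 2.3 expected; numerical excess in the intervention arm in 40% of trials; significant in 0.7%.
- δ = 0.5 points: 0.015 × 229 = 3.4 against 2.3; excess in about 60%; significant in 2%.
- δ = 1 point: 0.02 × 229 = 4.6 against 2.3; excess in 76%; significant in 6%.
- δ = 1.5 points: 0.025 × 229 = 5.7 against 2.3; significant in 12%.
- δ = 2, 3 and 5 points: 6.9, 9.2 and 13.7 against 2.3; significant in 21%, 43% and 81%.

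With p_C = 2%, increments of 2, 3 and 5 points give 16%, 32% and 69%.

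**What the increments imply.** If the extra visits are real episodes missed in controls, controls record p_C/(p_C + δ) of what the intervention arm records. That is 1/1.5 = 67% and 1/2 = 50% for 0.5 and 1 point, but only 1/3 = 33% to 1/6 = 17% for 2 to 5 points.

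**Alternative parametrisation.** Take a true risk of 3% in both arms and assume controls detect 50% of episodes (0.03 × 0.5 × 229 = 3.4). Intervention detection of 60%, 75% or 90% gives 4.1, 5.2 or 6.2 recorded events, an apparent risk ratio of 0.6/0.5 = 1.2, 0.75/0.5 = 1.5 or 0.9/0.5 = 1.8. A numerical excess then occurs in 53%, 66% or 77% of trials (42% with equal detection) and a significant excess in 1.6%, 3.8% or 7.4% (0.7% with equal detection).

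Both parametrisations point the same way: a misleading numerical excess becomes common under modest assumptions, while a significant one needs large ones.

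**The case against.** **The size is assumed.** No rate of reading-prompted visits is given. A reader might infer from the 21% to 81% figures that a false significant finding is likely. The protocol does not support that: with a 1% or 2% control rate, increments of 2 to 5 points put the intervention arm at 3% to 7% for hypotensive crisis alone, at or above the protocol's expectation for the combined endpoints. This objection stands.

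**A low reading is not a crisis.** A visit counts only if it is due to a hypotensive crisis, and section 10 c) lists such crises among serious events. A low home reading, or the routine appointment after a self-adjustment, does not by itself qualify. That limits the bias but does not remove it, because no criterion separates the two. The unmasked physician's review of the history is for relation to the intervention, not to confirm the event.

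**The contrast may be smaller than it looks.** The notebook's instructions for low readings are not shown. Controls are not barred from self-measuring, and section 4 describes home measurement as extensively practised. Home monitoring might also avert crises, so the net direction of the observed difference is open. All of this stands.

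**Consequences are limited.** The endpoint is tertiary. A reader might infer that detection-only visits would dominate the combined endpoint, but section 10 c) does not define its components and Table 4 lists the events individually. A reader might also infer that an artefact could stop the trial under section 12.6. That rule concerns serious events related to the intervention, and section 6.7 plans no interim analysis for safety, so this route is not established.

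**Conclusion.** The concern holds as a difference in detection built into the collection rule. Hypotensive crisis alone among the listed events adds outpatient visits, and home measurement and reading-driven contact are trial procedures in one arm only. Recorded outpatient events can therefore be more frequent under self-titration at equal true risk.

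The size cannot be derived from the protocol. Under a 1% control rate and an assumed 0.5 to 1 point of detection-only visits, the realistic consequence is a misleading numerical excess, with statistical significance uncommon. The outpatient component is affected most and emergency attendance possibly; admissions are hardly affected and deaths not at all. With at most about 7 patients per arm expected for the combined endpoints, a few such visits can still change how the safety comparison reads.

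**What to change.** In Table 4 (section 9.1) and section 10 c):

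1. Use one definition of hypotensive crisis for both arms that requires a clinician-recorded blood pressure or symptoms. The clinical criterion is for the sponsor to set.
2. Present the between-arm comparison by setting. Admissions and emergency attendances form the main line, as the component less dependent on home monitoring. Outpatient and telephone contacts form a separate line.
3. Add one field to the data collection notebook for whether a home reading prompted the contact. Apply it to emergency visits too, since a home reading can also prompt those.
4. Add a sensitivity comparison that excludes contacts prompted only by a home reading.

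The cost is some wording, one extra field, and fewer events in the main line. Dropping outpatient events from the comparison altogether would go too far, because some will be genuine harm from self-titration. With separate lines, all events are still reported. The change reduces the detection difference but does not eliminate it.
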